***HPV Sub-Study***

***Eligibility:*** Screen-positive women treated for pre-cancerous lesions of the cervix who are willing to be followed up for 6 months

***Visits:*** *Visits will take place on Day one of treatment with follow up at one week and 6 months post treatment.*

At enrollment, we will abstract data from medical files. Demographic and reproductive health information will be collected. HPV cervical swabs will be taken on Day 1 prior to treatment by the primary provider at the clinic.

We will obtain HPV swabs for all screened patients (+ve or -ve) and store them as we seek resources for testing. This will allow us to have quality swabs for assessment at the screen and test visit. Women who undergo ablative therapy will be asked to return a week later to make sure they are healing well. They shall be asked questions on whether they have abdominal pain, vaginal discharge or bleeding or any complication after treatment. This is routine for all women who receive treatment as part of their regular care. At 6 months post treatment, the participants will be asked to come to the clinic to be examined and to confirm that the abnormal changes are cleared. The six-month post treatment HPV test will assess clearance of HPV infection as a proxy cure and quality of implementation. HPV samples will be shipped to laboratories a Kenya based STI Laboratory, Ganjoni, Mombasa Kenya for testing. HPV results will be provided to participants to support their on-going medical care.

The shipped samples will be stored until the testing and analysis is complete. This will be done within two years of completion of all participants follow up.

At interval periods, we shall randomly sample 20 women (two per clinic) who undergo treatment for precancerous lesion with thermal ablation for an in depth interviews.

*Retention:* Women enrolled in the HPV sub-study will be requested to provide locator information, which will include an additional contact person. The study staff will call the participants one week after treatment to assess for wellbeing and an additional call to remind them of the upcoming month 6 visit.

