Thermal ablation has comparative advantage over cryotherapy (Table 2), it can be recharged with either electricity, solar-energy or even a car battery, treatment is shorter than cryotherapy (20-45 seconds per application), the instrument is small with portable options,(32) has minimal infrastructure requirements, probes are easy to sterilize and treatment can be completed by mid-level providers in primary care settings.(13) Thermal ablation has well documented outcomes, was commonly used in the Europe, especially the UK, for treatment of cervical precancerous lesions among other gynecological conditions in the 1980s. A metanalysis of thermal ablation by Dolman et al. in 2013, and an updated 2018 review by Randall et al., which included publications from LMICs, found cure rates of 94% for CIN2+ with treatment using thermal ablation (Table 1).(33)^,^(17) Reported side effects were mild to moderate and similar to cryotherapy, with vaginal discharge lasting 1-3 weeks, and mild pain post procedure and the majority reporting no side effects. Results from a more recent randomized clinical trial conducted in Zambia by a member of our investigative team(13) ([name]) and colleagues, revealed similar cure rates among women treated with thermal ablation (64%), cryotherapy (60%) and in the LLETZ (67%), as evaluated by assessing clearance of HPV infection 6 months after treatment.(16) Complaints of pain were document in approximately 2% of patients across treatment groups and no pain in the thermal ablation group were noted 2 weeks after procedure. More recent data from Western Kenya, found TA acceptability at 99%(16). This cumulative evidence has led to the adaptation of thermal ablation as treatment for pre-cancer lesions of the cervix and inclusion of thermal ablation as standard of care as recommendation by the 2019 WHO guidelines.(14)

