**Table 4: Summary of outcomes, by RE-AIM domain**

| RE-AIM Domain | Outcomes | Data source |
| --- | --- | --- |
| REACH | - Proportion of providers trained, and women screened per month | - Abstracted client records - Facility level data |
| EFFECTIVENESS | - Number of women screen-positive per month - Treatment completion rate among screen-positive women compared to pre-intervention (Primary) - Proportion of women with clearance of HPV 6 months post receiving TA treatment | - Facility level data - HPV test results from randomly selected women |
| ADOPTION | - Proportion of selected clinics incorporating thermal ablation into routine care through updated policies - Proportion of trained providers performing SVA_SAT +TA - Facility readiness | - Facility level data, Technical assistance reports - ORIC scores |
| IMPLEMENTATION | - Core components of the SVA-SAT+TA - Description of drivers of success/failure using CFIR constructs of interest | - Facility level data, Technical assistance reports - Key informant interviews |
| MAINTENANCE | - Proportion of clinics that continue to provide and sustain SVA-SAT+TA services 12,18 and 24 months after intervention implementation | - Facility level data |

- **EFFECTIVENESS** is a clinic and individual level measure that refers to whether the intervention had intended and unintended effects. We will determine whether the intervention is associated with a change in the number of screen-positive women identified per month and a substantial increase in treatment completion rate, comparing pre-and post-intervention periods.

Through an HPV-sub study, we shall assess fidelity of implementation of TA techniques by assessing for HPV clearance. We will collect HPV cervical swab prior to and 6 months post treatment to assess for clearance of type-specific HPV infection (target 60% HPV clearance) post-treatment on an estimate of 360 screen positive women treated with TA. HPV samples will be shipped to the UW/UON HIV/STD Research laboratory in Mombasa.

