**Power and sample size** According to data on cervical cancer screening and preventive treatment for Kiambu County from 2017-2019, 20% of cervical cancer screening clients who screened positive received cryotherapy or LEEP. Routine data from our proposed study facilities show an average of 30 clients per month were screened at each facility in the first three months of 2020 (**Table 3**), corresponding to approximately 10% of eligible clients. The primary effectiveness outcome is the proportion of screen-positive women who receive same day ablation treatment. Assuming six-month waves, 30 clients screened per month and a 5% screen positive rate, we will have an average of 9 screen-positive women per facility per wave. Assuming an intracluster correlation coefficient of 0.2, alpha=0.05 and 20% treatment coverage pre-intervention, we will have 80% power to detect a three-fold increase to 60% treatment coverage using thermal ablation (R (v 3.6.3) package swCRTDesign (v 3.1)). We estimate that 90% of screen positive women will be eligible for ablative treatment.(49)

**Data analysis**: The primary analysis of proportion of screen positive women who are treated pre vs post- intervention. We will use weighted least square methods appropriate for this facility-randomized three-wave step wedge design, where all clinics begin in the control condition, We will consider the intervention effect to be fixed throughout the exposed period, but random effects per facility and wave. To analyze secondary outcomes of increase in proportion of trained providers (the **REACH** outcome) and increase in number screen-positive (secondary outcome) we will use the same analysis approach for the binary and count outcome. Exploratory analysis will examine potential effect modification of facility-level factors such as patient volume, patient to provider ratio, and women screened. Potential multi-level adjustment variables include individual-level factors such as age and access to resources. The HPV sub-study in women treated with TA will assess HPV clearance in HPV-positive women. Assuming 70% of screen-positive women test positive for HPV prior to TA (N = 140), the confidence interval for HPV clearance will be +/-8.1%

- **ADOPTION**

Our primary outcomes for adoption will be

1. the proportion of clinics incorporating TA into routine care through updated policies
2. Proportion of trained providers performing SVA-SAT +TA for screen positive women and

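### The month-6 lesion examination is already planned but is not an outcome, so cure after thermal ablation rests on HPV clearance in the assumed 70% of women who are HPV-positive

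*Protocol*

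**What the plan says.** **Outcome lists.** Three places name a patient-level result of TA treatment: Objective 2(b) in the Executive Summary, the Effectiveness row of Table 4 (outcomes by RE-AIM domain), and the data-collection list in the Data section. In each it is HPV clearance at 6 months. The Effectiveness text says "we shall assess fidelity of implementation of TA techniques by assessing for HPV clearance", with "target 60% HPV clearance) post-treatment on an estimate of 360 screen positive women treated with TA". The HPV Sub-Study section openly calls the month-6 HPV test a proxy for cure and for quality of implementation.

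**Analysis set.** The Data analysis paragraph narrows this: "The HPV sub-study in women treated with TA will assess HPV clearance in HPV-positive women". It continues "Assuming 70% of screen-positive women test positive for HPV prior to TA (N = 140"), and then "the confidence interval for HPV clearance will be +/-8.1" percent.

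**The examination.** The HPV Sub-Study section gives the month-6 visit a second purpose: "the participants will be asked to come to the clinic to be examined and to confirm that the abnormal changes are cleared". Eligibility for the sub-study does not depend on the baseline HPV result, so HPV-negative women are followed to this visit too.

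**Other checks on technique.** The Training phase requires each trainee to be observed performing procedures and certified. The Intensive implementation phase adds bi-weekly visits by technical assistants, with fidelity assessment for 6 to 12 months.

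**The concern.** A woman with no HPV before treatment has no infection to clear. Her result says nothing, on this outcome, about whether treatment worked. The direct observation that could speak for her is due at the same visit as the HPV swab, but it appears in no outcome list and in no analysis.

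Two things are at stake. First, the report of cure would rest on a proxy in part of the treated group. Second, an examination that is not an outcome has no stated method, reader or data field, so it may not be recorded in a form that can be summarised later. Aim 3 also draws on Aim 2 effectiveness data to model CIN2+ and cancer cases, and HPV clearance is the only post-treatment measure of cure that Aim 2 lists.

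**Working it through.** **Inputs**
- HPV-positive share before TA, 70%; N = 140; half-width 8.1 points (Data analysis).
- Clearance target 60%; sub-study size 360 (Effectiveness text; Study Population).
- TA cure of CIN2+, 94% (Background). Used below only as an assumed value for lesion clearance, with 85% as an assumed lower value.

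**1. The plan's own precision.** Half-width = 1.96 × √(p(1 − p)/n).
- p = 0.60, n = 140: 1.96 × √(0.24/140) = 0.0812. The stated 8.1 points is reproduced.
- N = 140 implies 140/0.70 = 200 women enrolled, not 360.
- With 360 enrolled, 0.70 × 360 = 252 are HPV-positive, and 1.96 × √(0.24/252) gives 6.0 points.

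**2. Women who give no information on cure**
- 360 enrolled: 0.30 × 360 = 108.
- 200 enrolled: 0.30 × 200 = 60.

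**3. Where each month-6 result is used**

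| Place in protocol | HPV clearance | Lesion examination |
| --- | --- | --- |
| Objective 2(b) | listed | absent |
| Table 4, Effectiveness | listed | absent |
| Data analysis | analysed in HPV-positive women | absent |
| Data section list | listed | absent |
| HPV Sub-Study visits | planned | planned |

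**4. Precision of a lesion outcome in all TA-treated sub-study women**

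| Assumed clearance | n = 360 | n = 200 |
| --- | --- | --- |
| 94% | 1.96 × √(0.0564/360) = 2.5 points | 1.96 × √(0.0564/200) = 3.3 points |
| 85% | 1.96 × √(0.1275/360) = 3.7 points | 1.96 × √(0.1275/200) = 4.9 points |

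All half-widths ignore clustering by clinic and loss to follow-up.

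**5. Do the cited rates favour one outcome over the other?** The sample per arm (two-sided 5%, 80% power) is [1.96√(2p̄(1 − p̄)) + 0.84√(p₁(1 − p₁) + p₂(1 − p₂))]² / (p₁ − p₂)².
- HPV clearance, 60% (cryotherapy) against 64% (TA): about 2,311 per arm.
- Lesion cure, 92% (cryotherapy, CIN2) against 93.8% (TA, CIN2+): about 3,195 per arm.

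Lesion cure separates the methods no better than HPV clearance, so this comparison gives no reason to prefer either. The case for the lesion outcome rests on steps 2 and 3 alone.

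**The case against.** The strongest reply is that HPV clearance is a declared design choice. The protocol calls it a proxy. It is a laboratory, type-specific result, and it matches the 6-month measure in the randomised trial from Zambia that the Background cites. The examination has no stated method, no histology is planned in the sub-study, and clinical procedures are done by facility personnel, so the people being judged may read the result. The primary outcome, treatment completion, is untouched. All of this stands. It is why the lesion result belongs beside HPV clearance and not in its place.

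It could also be said that an analysis plan, or the abstraction of clinical outcomes related to treatment, will cover the examination. That abstraction item is undefined, and an analysis plan cannot rely on a result that the protocol does not require to be recorded.

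A reader might infer three stronger points, none of which the documents support:
- **That TA technique is judged only by HPV clearance.** It is not: observed proficiency, certification and fidelity assessment are also planned. The word only holds for cure and for the listed patient-level outcomes.
- **That HPV clearance cannot tell good TA from poor**, because the cited trial found 64%, 60% and 67% for TA, cryotherapy and LLETZ. Those figures compare three treatment methods. They say nothing about good against poor TA, and the sub-study has no comparison arm.
- **That the 60% target could be met with a given share of ablations ineffective.** This needs a clearance rate without effective treatment, which the protocol does not give, and it treats 64% as the result of perfect ablation.

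**Conclusion.** The point holds as a low-cost improvement. A direct observation of treatment result is scheduled and left unused, while the only listed outcome for cure leaves out about 30% of TA-treated sub-study women: 108 of 360, or 60 of 200. The 30% rests on the plan's own assumption of 70% HPV positivity, and the counts on which enrolment figure is right.

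The examination's accuracy as an outcome cannot be judged from the protocol, because its method is not stated. The precision shown for a lesion outcome depends on assumed clearance of 85 to 94%. The 94% is a published CIN2+ cure rate, not a rate for this visual reading. Nothing here requires the 60% HPV target to be dropped.

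**What to change.** - In Objective 2(b), the Effectiveness row of Table 4 (RE-AIM outcomes), the Data analysis paragraph and the Data section list, add a secondary descriptive outcome: the proportion of TA-treated sub-study women with no visible lesion at the month-6 examination, whatever their baseline HPV result.
- In the HPV Sub-Study section, state how the examination is done and record the result and who read it.
- Report the number examined and the proportion with its confidence interval, beside HPV clearance.
- Keep HPV clearance and its 60% target as a proxy, read together with the proficiency and fidelity assessments in the Training and Intensive implementation phases.
- Reconcile N = 140 (200 enrolled) with 360 enrolled (252 HPV-positive), and restate the half-width to match.

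The cost is protocol wording and recording the result and its reader at a visit already planned, with no new visit, test or staff. The downside is a visual reading without histology, possibly made by facility staff whose technique is being judged. Recording the reader makes that visible but does not remove it.

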**Aim 3: To compare the cost and budget impact of SVA-SAT+TA to SVA-SAT using cryotherapy*.***

We will quantify and compare the costs of SVA-SAT with thermal ablation to the costs of the current recommended standard practice of SVA-SAT with cryotherapy. Using micro-costing techniques, we will estimate the programmatic costs of each strategy, including implementation costs. We will use these data to estimate the cost per woman treated under each strategy, and we will incorporate reach and effectiveness outcome data (from Aim 2) in a decision analysis model to estimate and compare the costs incurred and averted. Cost and impact data will be used to estimate the budget impact of SVA-SAT with each treatment strategy. Our primary analyses will take the programmatic perspective, and secondary analyses will include costs incurred by patients to access services and duration of time used by providers to provide services. Our approach, analyses, and results reporting will align with published economic evaluation guidelines, which will maximize the transparency and generalizability of our findings to other settings.(68, 69) We hypothesize that SVA-SAT+TA will cost less per woman treated and will increase the affordability, feasibility and impact of cervical cancer prevention relative to SVA-SAT with cryotherapy.

**Table 4. Summary of cost measures and associated data sources**

| **Cost type** | **Elements** | **Data sources** |
| --- | --- | --- |
| Start-up | Training materials; training expenses (trainer fees, staff time spent in training) | Project expense reports; project staff / civil service salaries |
| Implementation | Ongoing training expenses; technical assistance support, facility committee meetings, fidelity monitoring; community outreach | Project expense reports |
| Personnel | Time/salaries of healthcare personnel, laboratory personnel, supervisors, and administrative staff | TDABC observations; staff interviews; civil service salaries |
| Patient | Transportation expenses; other out-of-pocket expenses, including childcare; time losses | Patient surveys; local average wages |
| Supplies | Consumables such as acetic acid, CO_2_ or N_2_O refrigerant gas, specula, anesthesia, equipment maintenance; transportation costs | Clinic and project expense reports; MOH records |
| Capital | Liger thermal ablator; cryotherapy machine; laboratory equipment; vehicles | Clinic and project expense reports; MOH records |
| Overhead | Utilities; clinic maintenance | Study clinic records and expense reports; staff interviews |

**Costing data collection.**

To capture heterogeneity in costs and efficiency across settings, *we will collect cost data in a representative sample of six RH clinics.* We will use an activity-based micro-costing approach to measure start-up, implementation, personnel, supply, capital, overhead, and patient costs in each clinic with standard practice (SVA-SAT with cryotherapy) and with implementation of SVA-SAT+TA (**Table 4**). Measured costs will include those incurred in the initial screening and treatment visit as well as follow-up visits. Following published protocols, we will observe clinic visits using time-driven activity-based costing (TDABC) methods to map out and quantify the time spent on each component activity.(70) We will also conduct semi-structured interviews with staff and key personnel to inform estimates of the time and costs required for provision of relevant SVA-SAT services. TDABC and interview data will be used to estimate the personnel time required for different cadres of personnel, which will be translated into costs based on average salaries. Start-up costs, ongoing implementation costs, and other program costs will be obtained from project expense reports, clinic records, Ministry of Health (MOH) records, and published literature, as in previous studies.(71-74) Patients will be asked about out-of-pocket expenses and time losses, with time losses translated into costs using data on local wages.

**Cost analysis.** We will summarize data on costs to estimate the total cost of SVA-SAT+TA per woman. Our micro-costing approach will allow us to identify and exclude costs specific to research activities, focusing only on programmatic costs. To reflect variable costs and activities in different phases of implementation of SVA-SAT+TA, we will stratify costs by initial start-up and maintenance phases. For each strategy, we will break costs down into the categories in Table 7, above, to identify the key cost drivers. Costs will be discounted at 3% per year, and we will explore alternative discounting rates of 5% and 0%.

**Budget impact analyses.** To account for differences in reach and effectiveness by treatment option, we will develop a decision tree model to estimate the expected number of CIN2+ and cervical cancer cases that would arise under a strategy of SVA-SAT+TA relative to SVA-SAT with cryotherapy given the size of the eligible patient population in Kenya. To estimate these health outcomes, we will incorporate study data on reach and effectiveness with each strategy (Aim 2) and published data on HPV natural history and progression to cancer. Costs will be estimated using study data on the cost per woman with each SVA-SAT intervention and published data of the costs of cervical cancer treatment and care. To account for variability and uncertainty in key parameters, we will conduct sensitivity analyses by jointly varying these parameters within observed or probable ranges. The model will be programmed using TreeAge Software (Williamstown, MA). Using data on current Kenya MOH expenditures, we will estimate the budget impact of the two interventions from the MOH perspective. This analysis will reflect the opportunity costs incurred by delivery of the SVA-SAT treatment strategies as well as costs averted through prevention of cervical cancer cases. Although cost-effectiveness analyses incorporating full societal costs are beyond the scope of the proposed grant, the cost and outcome data we collect can be used for such analyses in future applications.

# **LAB PROCEDURES**

We will conduct HPV DNA genotyping using the Roche Linear array assay (which can detect 37 HPV types) with a LOD of 50 copies, or equivalent PCR assay, ideally in real-time and in Kenya. HPV samples will be shipped to laboratories a Kenya based STI Laboratory ,Ganjoni, Mombasa Kenya for testing.

HPV DNA testing will be conducted using PCR. Exfoliated cell samples are digested with 20 μg/ml protease K at 37°C for one hour. DNA is isolated using the QIAamp DNA blood mini column (Qiagen, Inc., Valencia, CA) according to the manufacturer’s protocol. Two µl purified DNA (equivalent to one 250th of each sample) are amplified in 50 µl PCR reaction and 10 µL of PCR products are dotted onto nylon filters and probed with both a biotin-labeled HPV generic probe and a biotin-labeled β-globin probe. Samples negative for β-globin DNA are deemed insufficient. Specimens determined to be HPV positive by generic probe are typed using the Roche Linear Array HPV genotyping test (Roche Molecular Systems, Inc., Alameda, CA) for 37 HPV types or similar HPV DNA genotyping test.

# **DATA**

The primary goal of this project is to develop a dissemination and implementation strategy to introduce SVA-SAT+TA and deliver the intervention in the reproductive health facilities at a scale

*Data Collection*

We will use computer-based or paper based data collection forms for research variables and link to medical records data captured through standard clinic systems (e.g. cancer of the cervix screening, intervention offered for the screen positive women). All data will be maintained in a secure location. Internal quality control reports will be run on a monthly basis.

We will use CFIR interview guide tool to assess barriers and facilitators to potential adoption, delivery and sustainment of the SVA-SAT + TA intervention

Baseline data collection on proportion of screen positive women getting treatment pre-implementation will be collected at least 6 months prior to initiation of the intervention

After initiation we will collect the following information

- Proportion of women screened per month
- Proportion of trained health care providers
- Treatment completion rates for screen positive women
- Proportion of women with clearance of HPV at month six post treatment (this will be done in a sub-study with approximately 360 women)
- Proportion of clinics that have incorporated TA into routine care
- Proportion of trained providers performing SVA-SAT+TA
- Description of drivers and facilitators using CFIR constructs of interest
- Proportion of clinics that continue to provide and sustain SVA-SAT+TA services 13, 18 and 24 months after implementation phase

*Analysis*

Qualitative analyses will identify and describe key themes and explore variation within themes. Descriptive content will be inductively assembled to form explanatory accounts.

